### Recruitment strategies

Women from a diverse range of socioeconomic and ethnic backgrounds will be recruited predominantly from Birralee Maternity Service, Eastern Health, for which University and Hospital ethics approvals have been granted.

### Procedure

#### The intervention

##### The Health Coaching (HC) Intervention

In addition to usual care, women in this group will take part in a HC Intervention program. Our specialized HC Intervention has two components: (1) one-on-one sessions with a Health Coach, and (2) educational group sessions lead by a Health Coach. Each of these components are described in more detail below and presented as a timeline in Table 1. The Health Coach is accredited with Health Coaching Australia and is a practicing Physiotherapist.

**Table 1 T1:** Overview of intervention timeline: Health coaching, education sessions and assessments

	Intervention *n *= 110	Education Alone *n *= 110
**Pregnancy**		

14-16 weeks	First assessment (baseline questionnaire measures), BMI, waist circumference	First assessment (baseline questionnaire measures), BMI, waist circumference

16-18 weeks	First one-on-one session with Health Coach (face to face; 1 hour)	Usual care

20 weeks	First 2 × 2 hour group education session	First 2 × 2 hour group education session

22 weeks	Second 2 × 2 hour group education session	Second 2 × 2 hour group education session

24 weeks	Second one-on-one session with Health Coach (over the phone; 30 minutes)	Usual care

28-30 weeks	Two brief follow-up phone health sessions, (15 minutes each)	Usual care

32 weeks	Second assessment (follow-up questionnaire measures)	Second assessment (follow-up questionnaire measures)

**Postpartum**		

6 weeks	Third assessment (follow-up questionnaire measures)	Third assessment (follow-up questionnaire measures)

6 months	Fourth assessment (follow-up questionnaire measures)	Fourth assessment (follow-up questionnaire measures)

12 month	Fifth assessment (follow-up questionnaire measures), BMI, waist circumference Interviews with 20 women	Fifth assessment (follow-up questionnaire measures), BMI, waist circumference Interviews with 20 women

##### One-on-one sessions

In the one-on-one component of the intervention, a HC will promote patient adoption of healthy lifestyle behaviors (nutrition, physical activity, energy levels for weight management and will address mood and body image issues that commonly arise during pregnancy). Two one-on-one sessions with a trained HC professional will be conducted to address motivational factors, identify potential barriers to adopting a healthy weight-management regime, and assist pregnant women to identify individually tailored solutions to overcome these barriers. The HC will aim to build long-lasting skills about decision making, problem solving, planning and mood management. In these two sessions, the first for one hour at 16-18 weeks gestation (face to face, in a consulting room at the maternity service) and the second for 30 minutes at 24 weeks gestation (via telephone), goals and an action plan will be established collaboratively to initiate health behavior change relevant to healthy weight-management. Readiness, importance and confidence levels will be monitored to ensure that each patient is actively motivated to make the chosen changes and has a reasonable level of confidence in achieving the set goals. The Health Coach will respond appropriately to varying levels of readiness, importance and confidence using well recognized motivational interviewing and solution-focused counseling techniques. These techniques will be augmented by specifically designed techniques as required in order to address cognitive barriers to health behavior change.

##### Follow-up telephonic health coaching sessions

Two brief follow-up telephone health coaching sessions, for 15-minutes each time, will support ongoing behavior change maintenance and progress toward healthy weight-management goals. These telephone sessions will take place anywhere between 28-30 weeks gestation depending on the woman's needs or preferences.

##### HC educational group sessions

In addition to the individual HC sessions, there will be 2 × 2 hour group education sessions that include the following key topics: dietary and physical activity guidelines in pregnancy; beliefs about pregnancy weight gain and body image; beliefs about postpartum weight loss and body image; mood changes during pregnancy; factors that protect a women against elevated depressive symptoms; and the negative consequence of postpartum weight retention for maternal and infant/child health. These group sessions will support behavior change processes begun in the initial individual session, and hence will incorporate HC; they will take place when women are 20 and 22 weeks gestation.

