#### Education alone

In addition to usual care, women in this condition will receive 2 × 2 hour education group sessions that provide factual information only; that is, there will be no HC incorporated into these educational sessions and an educator, not the Health Coach, will run these sessions. The educator is a qualified workplace trainer and assessor.

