### Power, sample size, and retention

Given that the primary outcome of the study is maternal BMI, we aim to detect a clinically relevant difference in BMI of 0.8 kg/m^2 ^at 12 months postpartum. This difference is in accordance with the New Life (style) RCT that is currently being conducted in the Netherlands [63], that targets weight advice, weight development, nutrition and physical activity habits, but fails to target motivational variables, behavior-change assistance or psychological factors, such as depressive symptoms, anxiety symptoms, and body image. Consequently, the required *n *to detect this difference with 80% power at *α *= 0.05 and a standard deviation of 2 kg/m^2^, is 110 women per group; we have adopted this SD because we will also be measuring weight objectively at baseline and 12 months postpartum, removing any bias associated with self-report. Allowing for attrition of 20%, we will recruit 264 women and randomly assign 132 women into the HC Intervention and 132 women into the Education Alone control group. Our estimate of a drop-out rate is conservative and based on our previous large longitudinal studies with pregnant women and multiple time points [21,23,64]. As in our previous longitudinal pregnancy studies, this attrition rate of 20% takes into consideration that 5-7% of women may be diagnosed with gestational diabetes, which we expect to occur at 24-26 weeks; these women will therefore not affect the intervention, because we will over sample. A permuted blocks randomized treatment allocation schedule, produced by computer algorithm, will be used for the randomization process. To facilitate retention, we will build rapport with the participants through a study website, a regular newsletter, telephone support and advanced notification of assessments.

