### Analyses

We will adhere to 'intention-to-treat' principles following CONSORT Statement guidelines to prevent introduction of systematic bias [48]. As such, baseline data will be secured prior to treatment allocation, missing values will be scrutinized to check for non-random distribution and primary analyses will be executed twice: once using observed data, and once using multiple imputation under multivariate normal assumptions using methods given by Schaffer [65], so that all participants will be analyzed in their allocated condition. Analyses of covariance (with "other relevant variables" from above as covariates) will test the between group differences in the primary and secondary outcomes at each assessment time point and across time points. The confounder-adjusted analysis of the proportion of women returning to pre-pregnancy weight at 12 months post birth in each group will be tested using a logistic regression model. The second hypothesis will be tested using hierarchical regressions and path analysis. In addition, to further clarify the direction of effects between two variables across multiple time points, cross-lagged panel analyses will be conducted, e.g., to determine whether the level of maternal activity/depressive symptoms is a cause or consequence of higher BMI. Finally, the interview transcripts will be analyzed using elements of phenomenology and thematic content analysis to determine barriers to adopting healthy behaviors for weight management and the support or resources that women find most useful in achieving their gestational weight gain/postpartum weight loss goals [25,66].

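### Both arms are treated in education groups, but the sample size and the named models make no allowance for correlation within groups

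*Protocol article*

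**What the plan says.** Allocation is by individual woman, in permuted blocks (Protocol article, Participants). Both arms then attend group sessions at 20 and 22 weeks (Table 1). In the coached arm, "there will be 2 × 2 hour group education sessions that include the following key topics" (HC educational group sessions); that section adds that these groups carry on the behaviour change begun in the individual session and include coaching. In the control arm, "women in this condition will receive 2 × 2 hour education group sessions that provide factual information only" (Education alone). One section describes a single Health Coach, the other a single educator.

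The section Power, sample size, and retention targets a "clinically relevant difference in BMI of 0.8" kg/m² at 12 months postpartum, "to detect this difference with 80% power at *α *= 0.05". With "a standard deviation of 2 kg/m^2^, is 110 women per group", the only further adjustment is for loss: "Allowing for attrition of 20%, we will recruit 264 women and randomly assign 132 women into the HC Intervention", with the same number in the control arm. No group size, ICC or design effect appears.

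Under Analyses, analyses of covariance "will test the between group differences in the primary and secondary outcomes at each assessment time point and across time points", with covariates taken from the list under Other relevant variables. Education group is not on that list. Return to pre-pregnancy weight is tested by logistic regression, again with no group term named.

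**The concern.** Women who share a session share its discussion, its timing and the way it was delivered. In the coached arm the group is part of the active treatment, so some correlation in outcome within groups is plausible. A standard ANCOVA or logistic regression treats every woman as independent. With a positive ICC, its confidence intervals are too narrow and its tests reject too often under the null. A sample size calculated the same way then overstates the power of a test that is done correctly.

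Spare sample size can make up for lost power. It cannot correct the type I error of an unadjusted test, which depends on the design effect.

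**Working it through.** **Inputs from the Power section:** difference 0.8 kg/m², SD 2 kg/m², alpha 0.05 (taken as two-sided, since the section does not say), power 80%, 110 per arm, 132 randomised per arm, 20% loss.

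**Inputs not in the document, assumed:** women per education group m = 5 to 20; ICC = 0.01 to 0.05; the same values in both arms.

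**1. The plan's own figure, independent women.** n per arm = 2 × (1.96 + 0.8416)² × (2/0.8)² = 98.1, so 99. The stated 110 is not reproduced, but it errs on the high side. At 110 per arm, SE = 2 × √(2/110) = 0.2697, and power = Φ(0.8/0.2697 − 1.96) = Φ(1.007) = 84.3%. After planned loss, 132 × 0.8 = 105.6 per arm remain and power is 82.8%.

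**2. Clustering formulas.**
- Design effect: DE = 1 + (m − 1) × ICC.
- Type I error of the unadjusted test: 2 × (1 − Φ(1.96/√DE)).
- Power of a cluster-adjusted test: Φ(0.8/(2 × √(2 × DE/n)) − 1.96).

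**3. Results.**

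| m | ICC | DE | Type I error, unadjusted test | Power, adjusted test, 110 per arm | Power, adjusted test, 105.6 per arm |
|---|---|---|---|---|---|
| 5 | 0.01 | 1.04 | 5.5% | 82.9% | 81.3% |
| 5 | 0.02 | 1.08 | 5.9% | 81.4% | 79.9% |
| 5 | 0.05 | 1.20 | 7.4% | 77.3% | 75.6% |
| 10 | 0.01 | 1.09 | 6.1% | 81.1% | 79.5% |
| 10 | 0.02 | 1.18 | 7.1% | 78.0% | 76.3% |
| 10 | 0.05 | 1.45 | 10.4% | 69.3% | 67.5% |
| 20 | 0.01 | 1.19 | 7.2% | 77.6% | 75.9% |
| 20 | 0.02 | 1.38 | 9.5% | 71.4% | 69.6% |
| 20 | 0.05 | 1.95 | 16.0% | 56.5% | 54.8% |

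These are normal approximations. At m = 10 there are about 11 groups per arm (110/10), so a small-sample correction would lower the adjusted power a little further.

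**4. Where 80% power is lost.**
- With 110 analysed per arm, the break-even DE is 110/98.1 = 1.12. That is an ICC of 0.12/(m − 1): about 0.030 at m = 5, 0.013 at m = 10 and 0.006 at m = 20.
- With 105.6 per arm, the break-even DE is 105.6/98.1 = 1.08, or an ICC of about 0.019, 0.008 and 0.004 at the same group sizes.

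**5. What the power columns describe.** They are for a test that uses the correct standard error. The unadjusted test rejects more often under the alternative: at m = 10, ICC 0.02 and 110 per arm, the figure is Φ(1.007/√1.18) = 82.3%. That gain comes with a 7.1% type I error, so it is not usable power at the 5% level.

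**The case against.** The strongest reply is that the harm is conditional. The document gives no ICC and no group size. Group contact totals four hours, the coached arm also has individual sessions, and the outcome used for power is BMI more than a year after the last group session. A near-zero ICC cannot be excluded. The ICC may also differ between BMI, mood, diet and activity. This stands. A reader might infer that the planned standard errors are definitely too small, or that power has definitely fallen below 80%; the document supports neither without an assumed ICC.

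Second, the 110 carries slack and tolerates a design effect up to about 1.12. That also stands for power, although nothing in the Power section says the slack was meant for clustering. It does nothing for type I error.

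Third, Analyses is a condensed paragraph that names model families. A statistical analysis plan that is not shown may add a group term or a robust variance. It would therefore go too far to say that the protocol commits to a wrong standard error. The sample size is different: it is fixed here from listed inputs, with one adjustment, for attrition.

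Finally, there is a more certain threat to power. Participants and Table 1 give 110 per arm as the number allocated, whereas the Power section randomises 132. If 110 are randomised and 20% are lost, 88 remain and power is 75.6% before any clustering. That is a separate inconsistency and does not settle this one.

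**Conclusion.** The point holds in conditional form. Treatment in groups is certain in both arms, and neither the sample size nor the named models allow for it. If the ICC is above zero, unadjusted tests exceed 5%. At an assumed 10 women per group and ICC 0.01 to 0.05, type I error is about 6.1% to 10.4%, and adjusted power with 110 per arm is 81% to 69%, against 84% under independence. With smaller groups and a low ICC, power stays above 80%. These figures rest on assumed inputs and show sensitivity; they do not estimate what will happen in this trial. The change is worth making because it is cheap and because group membership may be hard to recover if it is not recorded when the sessions run.

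**What to change.** 1. Record an education-session group identifier for each woman, for both sessions. The document does not say that membership stays the same from the first session to the second, so the definition of a group should be written down.
2. In Analyses, state that between-arm outcomes are analysed with either a random effect for session group or a small-sample-corrected cluster-robust variance, for the continuous and the binary outcomes. Keep women who attend no group in their allocated arm as single-member clusters. With about 11 groups per arm, a simple form is enough; separate group variances by arm would be weakly estimated.
3. In Power, sample size, and retention, state the expected group size and an assumed ICC, and give power as a range, for example as in the table above.

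The cost is one extra variable, a few lines of text, somewhat wider confidence intervals and a stated power that may fall below 80%. The analysis change needs no extra women, but it does not restore 80% power across the range: at m = 10 and ICC 0.05, 98.1 × 1.45 = 142.3, so 143 analysed per arm would be needed.

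One limit remains. If each arm has a single provider, as the wording suggests, provider is confounded with arm and a group term cannot separate the two.

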#### Education alone

In addition to usual care, women in this condition will receive 2 × 2 hour education group sessions that provide factual information only; that is, there will be no HC incorporated into these educational sessions and an educator, not the Health Coach, will run these sessions. The educator is a qualified workplace trainer and assessor.

### Measures

Women will meet with researchers at 14-16 weeks gestation to collect demographic information (including pre-pregnancy BMI) and obtain anthropometric measurements (BMI and waist circumference). Women will also be given a copy of the US IOM gestational weight gain guidelines [9] and baseline measures of motivation, importance, confidence and readiness to adopt healthy lifestyle behaviors for weight management, perceived social support, depressive symptoms, body dissatisfaction, dietary habits and physical activity will be collected by questionnaire. Follow-up assessment of measures will take place at 32 weeks gestation, and at 6 weeks, 6 and 12 months post birth, with the exception of anthropometric measures which will be assessed at baseline and at 12 months post birth.

All measures in the questionnaire, with the exception of the first 14-16 week assessment session, will be collected in one of two ways: (1) via self-report questionnaires sent to the home of women with a request to return completed questionnaires (that will take no more than 30 minutes to complete) to the researchers in reply-paid envelopes provided to them; (2) by researcher interview over the phone. Women will be able to choose the method of data collection that suits them best. Anthropometric measures will be obtained in person by trained research staff.

### Primary outcomes

#### BMI

Height will be measured by researchers with a stadiometer at the first and last assessments (14-16 weeks gestation and 12 months postpartum) for both groups. Women will be weighed each time wearing light clothing and no shoes. Pre-pregnancy weight will be based on self-report; weight at 14-16 weeks gestation and 12 months postpartum will be measured by the researchers using electronic scales. Height and weight measurements will be used to calculate BMI (kg/m^2^). At all other assessment time points, women will be encouraged to consult with their healthcare professional to provide additional objective weight measurements (including the last weight reported prior to delivery), and in the postpartum we will ask women to be weighed at their Maternal and Child Health appointment. Women will record these measurements in a 'weight passport' provided by researchers.

Waist circumference will be measured by trained researchers using a standard tape measure when height and weight measurements are obtained.

### Secondary outcomes

All the measures below will be measured at each of the assessment time points noted in Table 1.

#### Readiness to change

A series of 10 questions developed by the researchers assess importance, readiness and confidence of women to change their diet and physical activity habits (i.e. "How important/confident/ready are you right now to take some action to manage your diet/physical activity habits to be healthy, given everything else that is going on in your life right now?"), along with a subjective rating of how healthy their diet and physical activity habits are (i.e. "On a scale of 0-10 please rate how healthy your feel your current diet/physical activity habits are"). Participants are asked to provide a rating on a scale from 0-10 (not at all - extremely) for each item.

#### Motivation to change

Three items developed by the researchers will assess importance, confidence, and motivation to initiate, and if initiated to maintain, healthy behavior changes.

#### General distress and psychopathology

Measures include the short form of the Depression Anxiety Stress Scale and the Edinburgh Postnatal Depression Scale. The Edinburgh Postnatal Depression Scale [56] cut-off scores between 12.5 and 13 result in excellent sensitivity and very good specificity for postpartum use compared to research diagnostic criteria.

#### Body dissatisfaction

The Body Attitudes Questionnaire is a multi-dimensional set of scales developed and validated in Australia; subscales related to body size dissatisfaction: Strength and Fitness, Attractiveness, Salience of Weight and Shape and Feeling Fat [57] will be used. The current and ideal versions of the Contour Drawing Rating Scales [58] will also be administered in the postpartum.

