## Methods/Design

### Overall study design

This study will be a randomized controlled trial (RCT) with pregnant women randomly allocated to either the HC Intervention or an Education Alone control group. The study will be conducted and reported in line with CONSORT recommendations [55]. Baseline assessment of study variables will occur at 14-16 weeks gestation; this allows women to consider the pregnancy certain (since the threat of miscarriage has substantially decreased) and to participate at a standardized time point. Follow up assessments will take place at 32 weeks gestation, and at 6 weeks, and 6 and 12 months postpartum. The study was approved by the Eastern Health Human Research Ethics Committee on the 25th March, 2011 (EH-HREC E40/1011) and Deakin University Human Research Ethics Committee on 21st April, 2011 (DUHREC 2011-087).

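### The Contour Drawing Rating Scales appear to be postpartum-only despite the all-waves rule, so they have no pre-randomisation value and the listed covariates supply no substitute

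*Protocol article*

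**What the plan says.** The Secondary outcomes section opens with a rule that has no exception: "All the measures below will be measured at each of the assessment time points noted in Table 1". Table 1 lists five assessments: 14-16 weeks and 32 weeks of gestation, then 6 weeks, 6 months and 12 months after birth. The Measures section also takes follow-up measures at every later wave and makes one exemption only: "with the exception of anthropometric measures which will be assessed at baseline and at 12 months post birth".

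The Body dissatisfaction section names two instruments. Four subscales of the Body Attitudes Questionnaire come first, with no limit on timing: "Strength and Fitness, Attractiveness, Salience of Weight and Shape and Feeling Fat [57] will be used". The second instrument is given a period: "The current and ideal versions of the Contour Drawing Rating Scales [58] will also be administered in the postpartum".

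The Analyses section says that analyses of covariance "will test the between group differences in the primary and secondary outcomes at each assessment time point and across time points". The covariates it names are those listed under Other relevant variables, such as parity, socioeconomic status, social support, coping style, and labour and breast-feeding experiences. No body-image score is among them.

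**The concern.** The general timing rule and the sentence on the contour scales do not fit together. If the specific sentence governs, the scale is first given at 6 weeks postpartum. That is after randomisation, after the coaching sessions (which run from 16-18 to 28-30 weeks) and after the 32-week assessment that follows them.

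Specific aim 2 is to trace how coaching acts on weight management in pregnancy and after birth, and it predicts lower body dissatisfaction. A scale that starts postpartum can contribute an arm difference after birth. It cannot contribute a change from before coaching or a path from pregnancy to postpartum.

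It also has no baseline of its own to adjust for, and the listed covariates offer no substitute. What is at stake is therefore precision, together with clarity about which instrument carries the analyses that cross birth.

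**Working it through.** No stated figure in the protocol bears on this point, so there is none to reproduce. The check has two parts.

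**1. Schedule, section against section**

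| Assessment | Contour scales under the general rule (Secondary outcomes) | Contour scales under Body dissatisfaction | Body Attitudes Questionnaire |
|---|---|---|---|
| 14-16 weeks (baseline) | yes | no | yes |
| 32 weeks | yes | no | yes |
| 6 weeks postpartum | yes | yes | yes |
| 6 months postpartum | yes | yes | yes |
| 12 months postpartum | yes | yes | yes |

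- Contour coverage on the natural reading is 3/5 = 60% overall, 0/2 in pregnancy and 3/3 postpartum.
- The other possible reading takes 'also' to mean postpartum as well as pregnancy. After the general rule that would add nothing, so it is the less likely one.
- The questionnaire column follows from the general rule. The Measures section supports it at the level of the construct, since it lists body dissatisfaction among the baseline questionnaire measures: "perceived social support, depressive symptoms, body dissatisfaction, dietary habits and physical activity will be collected by questionnaire". It does not name the instrument there.

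**2. Precision given up without a baseline body-image covariate (illustration)**

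Inputs:
- r, the correlation between the baseline Body Attitudes Questionnaire score and the postpartum contour score. The protocol gives no value, so 0.3, 0.5 and 0.7 are assumed.
- 110 women analysed per arm, 80% power and α = 0.05, from Power, sample size, and retention; α is taken as two-sided.
- The other listed covariates are ignored. If they explain part of the same variation, the relevant r is what remains after them.

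Formulas:
- Variance of the arm difference, unadjusted over adjusted = 1/(1 − r²).
- Detectable difference in SD units, unadjusted = (1.960 + 0.842) × √(2/110) = 2.802 × 0.1348 = 0.38.
- Detectable difference, adjusted = 0.378 × √(1 − r²).

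| Assumed r | 1 − r² | Variance ratio | Detectable difference, adjusted (unadjusted 0.38 SD) |
|---|---|---|---|
| 0.3 | 0.91 | 1.10 | 0.36 SD |
| 0.5 | 0.75 | 1.33 | 0.33 SD |
| 0.7 | 0.51 | 1.96 | 0.27 SD |

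These figures measure the effect of adding a covariate that is already collected. They do not measure an error in the planned comparison.

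**The case against.** The strongest reply is that this is a one-clause slip. A specific sentence in the same section qualifies a general one, and introducing a body-figure scale only after birth may well be deliberate. The phrase about testing at each time point cannot mean five waves for every outcome, because waist circumference sits under Primary outcomes and is measured only at baseline and 12 months. It must mean the waves at which a measure is taken. On that reading the Analyses section does not conflict with a postpartum-only scale.

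That reply stands, and it rules out four stronger readings that a reader might infer:

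- **The scale cannot enter the across-time analyses.** Three postpartum waves are enough for arm comparisons at each wave, an analysis across those waves and a postpartum cross-lagged model.
- **Body dissatisfaction has no baseline.** It has one as a construct under Measures, and the Body Attitudes Questionnaire falls under the all-waves rule.
- **The postpartum comparison is biased.** Randomisation keeps it valid without adjustment.
- **A change of instrument distorts the trend.** Nothing in the protocol combines the two instruments into one score.

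A further reply is that the precision loss does not come from the timing. The protocol names no outcome's own baseline as a covariate, and such detail is often left to an analysis plan. This stands in part. For the other secondary measures, an analysis plan can add the outcome's own baseline as a matter of convention. For the contour scales no such value will exist, so a substitute has to be chosen. The protocol does name a covariate set, and that set contains no candidate.

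**Conclusion.** The inconsistency between the Secondary outcomes and Body dissatisfaction sections is real, and its consequence is small. It concerns a supplementary scale for one secondary outcome. It does not touch the primary outcomes, the sample size or Specific aim 1, and Specific aim 2 can still be pursued through the Body Attitudes Questionnaire.

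The practical gain is in precision. It ranges from slight at r = 0.3 to substantial at r = 0.7, where the adjusted variance is about half the unadjusted one. This rests on the postpartum-only reading, on the questionnaire being given at baseline, and on correlations that are assumed. Reconciling the two sentences alone would be clerical; the adjustment is what makes the change worthwhile.

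**What to change.** 1. In Secondary outcomes, except the Contour Drawing Rating Scales from the all-waves rule and state that they are given at 6 weeks, 6 months and 12 months postpartum. If all five waves were in fact intended, correct the Body dissatisfaction section instead.
2. In Analyses, state that the arms are compared on the contour scales at those three waves and across them, with the baseline Body Attitudes Questionnaire score as a covariate. Name in advance which of the four subscales is used, or that all four are.
3. State that analyses spanning pregnancy and postpartum, including path and cross-lagged models, use the Body Attitudes Questionnaire for body dissatisfaction.

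The cost is wording only. The baseline questionnaire is already in the schedule, so no visit, item or participant is added. Settling this before the data are seen also removes a later choice of instrument or time window.
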